## Abstract

**Background::**

Pyogenic osteomyelitis of the spine usually occurs in patients over 55 years old with acute osteomyelitis. Surgical treatment and fixation can relieve pain, enhance spinal balance and nerve function, so that patients can walk as soon as possible. Different outcomes of surgical methods include anterior minimally invasive oblique retroperitoneal approach (ORA) and posterior transpedicular approach (PTA). While, there is no consensus on the best treatment for PVO. The goal of the protocol is to compare the clinical consequences between PTA and ORA for treating PVO.

**Method::**

The experiment is a single-center randomized clinical research. This experiment was admitted by the Ethics Committee of the People's Hospital of Dayi County (Approval number: 1002-084). In all, 50 patients with lumbar vertebral osteomyelitis (LVO) who prepares surgical treatment will be included in the study. We contain adult patients (aged over 18 years) who accept debridement and spinal stabilization with LVO. Cases are removed if there is previous hardware placement, cases who are not confirmed by microbiology, or severe renal and liver dysfunction. The primary outcomes are intraoperative blood loss, operative time, hospital stay, primary failure and recurrence, and bone fusion. The secondary outcomes are postoperative pain score and physical recovery. SPSS Sample Power version 3.0 (IBM, Armonk, NY, USA) is used for data analysis.

**Results::**

Table 1 will show the outcomes in both groups.

**Conclusion::**

This protocol may offer a reliable basis for the effectiveness of the two approaches in the treatment of PVO.

**Trial registration number::**

researchregistry6046

## Introduction

1

Pyogenic vertebral osteomyelitis (PVO) is common in acute osteomyelitis over 55 years old.^[1]^ The incidence rate of PVO in high income countries has increased gradually, increasing from 4 to 10 people in each 100 thousand population.^[2,3]^ Patients with PVO often present with nervous system damage, persistent infection and distortion.^[4,5]^ If the patient is diagnosed with early PVO, conservative treatment can obtain good results.^[6,7]^ However, patients with progressive physical instability pain, epidural abscesses, neurological damage, and antibiotic failure often need surgical operation. More and more surgeons realize that surgical treatment and fixation can reduce pain, improve spinal balance and neurologic, and lead to initial ambulation.

This paper introduces the different results of anterior minimally invasive retroperitoneal oblique approach (ORA) and posterior transpedicular approach (PTA) debridement. The ORA has the following advantages, such as less impact on nervous system, and relatively consistent access to the lower lumbar levels.^[8]^ However, in some cases involving high riding pelvis, access to the lower lumbar level is limited. Therefore, in order to perform lumbar interbody fusion from L1 to S1, the surgeon needs to separate the incision or change the position. PTA surgery is gradually accepted by surgeons. Some surgeons claimed that single-stage debridement and instrumented interbody fusion can eliminate local diseases, reduce nerve pressure, and rectify spinal malformation in single-stage surgery with smaller trauma, fewer complications, lower cost and shorter rehabilitation time.^[9,10]^ While the best treatment of PVO is still controversial, and there are few reports about it. The aim of the protocol is to compare the clinical outcomes between PTA and ORA for treating PVO.

## Materials and methods

2

The experiment will be implemented from December 2020 to December 2021 at the People's Hospital of Dayi County, in accordance with the purposes of the Declaration of Helsinki. The experiment was admitted by the Research Ethics Committee of the People's Hospital of Dayi County (Approval number: 1002-084) and recorded in research registry (Identifier: researchregistry6046). The experiment is a single-center randomized clinical research. The recruited patients provide written informed consent prior to enrollment.

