### Inclusion and exclusion criteria

2.1

In all, 50 patients with lumbar vertebral osteomyelitis (LVO) who prepares surgical treatment will be included in the study. We include adult patients (aged above 18 years) who accept debridement and spinal stabilization with LVO. LVO has three characteristics: symptoms (back pain, fever and reduced lumbar range of motion), X-ray (vertebral and intervertebral disc lesions), and bacterial pathogens (confirmed by laboratory tests). All patients have intact medical reports. Cases are removed if there is previous hardware placement, cases who are not confirmed by microbiology, or severe renal and liver dysfunction. All patients are followed up for at least 12 months.

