### Outcomes

2.3

The primary outcomes are intraoperative blood loss, operative time, hospital stay, primary failure and recurrence, and bone fusion. The secondary outcomes are postoperative pain score and physical recovery. Patient Reported Outcomes Measurement Information System^[11]^ are used to evaluate physical function.

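### The stated trial dates (December 2020 to December 2021) and 12 months or more of follow-up for all 50 patients cannot both be met: the window leaves between no time and about 31 days for recruitment

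*Protocol article*

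**What the plan says.** Section 2 (Materials and methods) of the protocol article dates the trial as a whole: "The experiment will be implemented from December 2020 to December 2021". It adds "The experiment is a single-center randomized clinical research" and "The recruited patients provide written informed consent prior to enrollment", so enrolment is prospective and no follow-up can build up before the window opens.

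Section 2.1 sets the sample size, "In all, 50 patients with lumbar vertebral osteomyelitis (LVO) who prepares surgical treatment will be included in the study", and the follow-up requirement, "All patients are followed up for at least 12 months".

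Section 2.3 lists five items as primary outcomes. Three are settled during surgery or the hospital stay. The other two need follow-up after discharge: "primary failure and recurrence, and bone fusion". Section 2.3 gives no assessment time for either.

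The article gives no separate recruitment period, no date for the last patient's last visit and no data cut-off.

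**The concern.** A trial that recruits over some period and then follows every patient for a year lasts as long as recruitment plus one year. The printed dates span roughly one year in total, so the follow-up requirement alone uses up almost the whole window.

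Two of the five primary outcomes depend on that follow-up. If the end date were applied as printed, late entrants would contribute little or no observation time to recurrence and fusion. Section 2.4 names only chi-square and t-tests, and neither takes account of patients having been observed for different lengths of time. The reader could not then tell a patient without recurrence from one who had not been watched long enough.

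**Working it through.** **Inputs.** Trial window: December 2020 to December 2021 (section 2). Minimum follow-up: 12 months for every patient (section 2.1). Sample size: 50, at one centre (sections 2.1 and 2). Incidence, used only as a plausibility check: "increasing from 4 to 10 people in each 100 thousand population" (Introduction). No time unit is printed, so reading this as a yearly rate is an assumption.

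**Step 1: time left for recruitment.** Recruitment room = length of window − 12 months (365 days).

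| Reading of the window | Length | Room for recruitment |
|---|---|---|
| Narrowest: 31 Dec 2020 to 1 Dec 2021 | 335 days | 335 − 365 = −30 days |
| Nominal: mid-December to mid-December | 365 days | 365 − 365 = 0 days |
| Widest: 1 Dec 2020 to 31 Dec 2021, inclusive | 396 days | 396 − 365 = 31 days |

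**Step 2: is the widest reading workable?** All 50 patients would have to enter within 31 days: 50 / 31 = 1.61 per day, or 1.61 × 365 ≈ 589 per year. At 10 cases per 100,000 per year that is every case from 589 / 10 × 100,000 ≈ 5.9 million people. At 4 per 100,000 it is 589 / 4 × 100,000 ≈ 14.7 million. Both figures come before any restriction to lumbar, surgically treated and microbiologically confirmed disease. For one county hospital this is a practical impossibility.

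**Step 3: what would be observed if data closed on 31 December 2021.** The article gives neither an accrual rate nor a cut-off, so both are assumptions here. With uniform entry over A months from 1 December 2020 and closure at 13 months, the share with 12 months of follow-up is 1/A, and the last patient has 13 − A months.

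| Accrual period A | Patients reaching 12 months (50 / A) | Follow-up of last patient |
|---|---|---|
| 3 months | 16.7, about 17 of 50 | 10 months |
| 6 months | 8.3, about 8 of 50 | 7 months |
| 13 months | 3.8, about 4 of 50 (7.7%) | 0 months |

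With 13-month accrual, mean follow-up is 13 / 2 = 6.5 months. Counting at most 12 months per patient, the mean is (12²/2 + 12 × 1) / 13 = 84 / 13 months. The share of the required observation time obtained is therefore 84 / (13 × 12) = 84 / 156 = 54%.

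**Step 4: duration that satisfies section 2.1.** The trial needs A + 12 months: 15 months for A = 3, 18 for A = 6, 24 for A = 12. If the printed dates are the recruitment period alone, follow-up of the last patient runs to about December 2022.

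**The case against.** The strongest reply is that the printed dates may cover only recruitment and surgery at the hospital, with follow-up running on afterwards. Nothing in the article calls December 2021 the end of follow-up, a data cut-off or an analysis date. If the follow-up sentence in section 2.1 governs, no observation time is lost, and the defect is only a wrong or incomplete end date. This stands as a limit on the consequences. It does not remove the conflict, because the sentence dates the experiment as a whole and no later date appears.

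A second reply is that an article condenses the full protocol, which may hold a proper schedule. That would answer a complaint about something missing. Here two printed statements disagree.

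Three stronger readings are tempting, and the article does not support them.

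- **That recurrence and fusion cannot be observed, or will be under-counted.** Section 2.3 sets no assessment time for either outcome, so there is no stated time point to miss. What can be shown is that not every patient could be observed for the stated 12-month minimum, and only if the trial closes on the printed date.
- **That the comparison between arms would be biased.** Arms randomised concurrently would be cut short alike on average. The expected harm is fewer observed events, early or missing fusion readings and lower precision.
- **That the 12-month floor must become a fixed 12-month outcome definition.** That is a separate matter of outcome definition, and it does not follow from the dates.

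**Conclusion.** The conflict between sections 2 and 2.1 is real and rests on calendar arithmetic alone. It is strict on the narrowest and nominal readings of the window. On the widest, it is a practical rather than a logical impossibility.

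The loss of data is conditional. It needs closure in December 2021 and an assumed accrual pattern. Under those assumptions between about 4 and about 17 of 50 patients would complete 12 months, for uniform accrual over 13 down to 3 months, so 33 or more would fall short. The loss would fall on primary failure and recurrence and on bone fusion. The three perioperative primary outcomes are largely unaffected.

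**What to change.** Reconcile sections 2 and 2.1 by stating two things separately: the recruitment period, and the end of follow-up, set at least 12 months after the last operation. If recruitment runs to December 2021, the end of follow-up is about December 2022. State also that recurrence and fusion are analysed only once the last patient has completed 12 months.

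The cost is a correction to the text and a later final analysis, by about a year if recruitment fills the printed window. No extra patients or procedures are needed. Whether the registry entry or ethics approval also needs changing cannot be judged from the article, since either may already carry a later end date; both should be checked against the corrected dates.

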### Inclusion and exclusion criteria

2.1

In all, 50 patients with lumbar vertebral osteomyelitis (LVO) who prepares surgical treatment will be included in the study. We include adult patients (aged above 18 years) who accept debridement and spinal stabilization with LVO. LVO has three characteristics: symptoms (back pain, fever and reduced lumbar range of motion), X-ray (vertebral and intervertebral disc lesions), and bacterial pathogens (confirmed by laboratory tests). All patients have intact medical reports. Cases are removed if there is previous hardware placement, cases who are not confirmed by microbiology, or severe renal and liver dysfunction. All patients are followed up for at least 12 months.

### Surgical approach

2.2

(1)Procedures of ORA: patients are set in lateral decubitus position (lesion characteristics determine right or left lateral decubitus position). The retroperitoneal space is entered through a small incision of four cm. After meticulous observation with a channel and microscope system, segmental vessels are carefully examined and ligated. Then, the edge of the lesion is inspected and debridement is constructed by curette, bone biting forceps and high-speed drill. We stop debridement until normal bleeding bone appears. For patients with epidural involvement, the focus is washing with a special infusion tube. After complete resection of the lesion, titanium or peek cages are implanted to fill the bone graft/substitute.(2)Procedures of PTA: the posterior midline straight incision is used, and the opposite side is treated with Wiltse paravertebral muscle splitting method. Place a rod to temporarily link with the screw. The lamina, facet, pedicle and proximal transverse process are excised. After meticulous observation, the vertebral body and intervertebral disc are excised by high-speed pedicle drill or bone knife to expose the normal bone endplate. After limited resection, titanium or peek cages are implanted to fill the bone graft/substitute. All patients are treated with percutaneous pedicle screw fixation.

### Outcomes

2.3

The primary outcomes are intraoperative blood loss, operative time, hospital stay, primary failure and recurrence, and bone fusion. The secondary outcomes are postoperative pain score and physical recovery. Patient Reported Outcomes Measurement Information System^[11]^ are used to evaluate physical function.

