### Statistical analysis

2.4

SPSS Sample Power version 3.0 (IBM, Armonk, NY) is applied to analyze data. Afterward, all the data are expressed with appropriate characteristics such as mean, median, standard deviation as well as percentage. Continuous and categorical variables are analyzed using χ^2^-tests and independent t-tests, respectively. Intention to treat analysis is applied to evaluate the outcomes. Significant level: *P* < .05.

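### Five or six unranked primary outcomes are each tested at P < .05; if any one of them is enough, the false-positive chance is about 13–26%, not 5%

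*Protocol article*

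**What the plan says.** Section 2.3 (Outcomes) gives the list: "The primary outcomes are intraoperative blood loss, operative time, hospital stay, primary failure and recurrence, and bone fusion". The Abstract repeats it. Postoperative pain and physical recovery are set apart as secondary, so the primary label is a deliberate choice. Nothing in the list is ranked or singled out. As punctuated there are five items. The fourth joins primary failure with recurrence and does not say whether they are one outcome or two.

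Section 2.4 (Statistical analysis) plans a separate univariate test for each variable: "Continuous and categorical variables are analyzed using χ^2^-tests and independent t-tests, respectively". (The two test types are attached to the wrong variable types as worded; that is a separate matter.) One threshold covers everything: "Significant level: *P* < .05". The text has no adjustment, testing order or joint test, and does not say whether one primary outcome or all of them must reach significance.

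On size and design, the article states "The experiment is a single-center randomized clinical research" and "In all, 50 patients with lumbar vertebral osteomyelitis (LVO) who prepares surgical treatment will be included in the study". It gives no allocation ratio, power or effect size.

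**The concern.** With several equal primary outcomes and one unadjusted threshold, the stated significance level applies to each test and not to the trial's conclusion. Either approach could be presented as better on whichever outcome crosses .05, and the choice could be made after the data are seen.

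Conflicting results are foreseeable here. The Discussion credits the oblique approach with shorter debridement and easier control of bleeding, and suggests that the posterior approach may be better for posterior decompression. One arm could therefore do better on operative time or blood loss and worse on infection control. The text names no deciding outcome for that case, yet the Conclusion expects the trial to give a dependable basis for judging the effectiveness of the two approaches. In a trial of 50 patients, a single nominally significant result among five or six is weak support for that.

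**Working it through.** **Inputs from the article.** Number of primary outcomes k = 5 as punctuated, or 6 if primary failure and recurrence are separate (section 2.3). Per-test level 0.05 (section 2.4). Total sample size 50 (section 2.1).

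**Assumptions.** Two-sided tests. Any one significant primary outcome counts as evidence for an approach. 25 patients per arm, used only in steps 3 and 5.

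The article states no overall error rate and gives no inputs from which the 50 could be rebuilt, so there is no figure of its own to reproduce first.

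**Step 1: independent tests.** The chance of at least one false positive when no outcome differs is 1 − (1 − 0.05)^k.
- k = 5: 1 − 0.95^5 = 0.226
- k = 6: 1 − 0.95^6 = 0.265

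The upper bound under any dependence is k × 0.05, that is 0.25 or 0.30.

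**Step 2: correlated tests.** Blood loss, operative time and hospital stay probably move together. Simulation of k equally correlated two-sided z-tests (400,000 draws):

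| Pairwise correlation | k = 5 | k = 6 |
|---|---|---|
| 0.3 | 0.209 | 0.241 |
| 0.5 | 0.183 | 0.208 |
| 0.8 | 0.127 | 0.139 |
| 0.9 | 0.102 | 0.108 |

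**Step 3: sparse binary outcomes.** At 25 per arm a chi-square test on a rare event has a true size below 0.05. The check used three continuous tests at 0.05, assumed failure or recurrence rates of 4% to 10%, assumed fusion rates of 80% to 95%, and independence between tests.
- Uncorrected chi-square: about 0.18 to 0.23 (k = 5) and 0.19 to 0.27 (k = 6)
- Continuity-corrected chi-square: about 0.14 to 0.17

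Every scenario run is at least twice the nominal 0.05. High correlation combined with continuity correction was not run and would come out lower.

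**Step 4: error rate after a fix.** One named primary outcome tested at 0.05 gives 0.05. Splitting the level equally gives 0.05/5 = 0.010 or 0.05/6 = 0.0083 per test. The overall error is then 0.049 under independence and at most 0.05 under any dependence. Holm starts at the same thresholds and has the same guarantee.

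**Step 5: cost in detectable effect (continuous outcomes only).** For a two-sample t-test with 25 per arm and 80% power, the detectable standardised difference is:
- level 0.05: 0.81 SD
- level 0.010: 1.00 SD
- level 0.0083: 1.02 SD

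The normal approximation (z for the level + z for the power) × √(2/25) gives (1.960 + 0.842) × 0.283 = 0.79 at level 0.05. At the two smaller levels it gives 0.97 and 0.98, the same pattern.

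**The case against.** The strongest reply is that the inflation depends on a decision rule that the article does not state. Its aim is to compare clinical outcomes, and it nowhere says that one significant result is enough. If every primary outcome had to be significant, the error would not be inflated. That is correct, and it is why the percentages here are conditional. But the all-must-win rule is not stated either.

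A second reply is that multiplicity rules are often left to an analysis plan, and only a condensed article is at hand. That disposes of any complaint that detail is missing. It does not dispose of what the article fixes: several equal primary outcomes and one threshold for all of them. A later plan could add an adjustment, but the published list and level would still need to be changed to match.

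Two stronger readings should be resisted. A reader might infer a flat one-in-four risk. That figure needs independent tests and an any-one-wins rule; with plausible correlation or conservative binary tests it is lower. A reader might also infer that primary failure and recurrence compete, so that the arm with more failures could look better on recurrence. The article defines neither term, joins them as a single item, and does not say that recurrence is tested alone. They may already be meant as one combined outcome, so the text does not support that argument.

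**Conclusion.** The point holds in conditional form. The article fixes five or six unranked primary outcomes and one unadjusted level of .05 for separate tests. If any single significant primary outcome is read as favouring an approach, the false-positive chance is about 23% (five) or 26% (six) under independence. It is roughly 13% to 24% at pairwise correlations of 0.3 to 0.8.

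Confidence is high on the structure, because it is what the text says. It is lower on the exact percentage, which rests on the unstated win rule, on an unknown correlation and on whether there are five or six tests. The matter needs settling before results are seen, because the trial's main conclusion depends on it.

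**What to change.** **Preferred.** In section 2.3 (and the Abstract), name one primary outcome and make the others secondary. The investigators should choose it before any outcome data are examined. This is a change of wording and costs no power relative to testing that outcome at .05. It also settles what the trial concludes if outcomes point in different directions.

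**Alternative.** Keep the list and state in section 2.4 that Holm is applied across it, with superiority claimed only on adjusted results. The first Holm test must reach P < .010 (five outcomes) or P < .0083 (six), with the loss of sensitivity shown in step 5. No corresponding figure is given for failure, recurrence or fusion, because the article states no rates. Holm controls the error rate but does not resolve conflict: two adjusted results can still favour different arms, so a sentence on how that would be interpreted is needed as well.

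**In either case.** State in section 2.3 whether primary failure and recurrence are one combined outcome per patient or two outcomes, so that the number of tests is fixed.

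### Pain and physical function are compared without the preoperative value; ANCOVA on that value would be a cheap gain in precision for these secondary outcomes

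*Protocol article*

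**What the plan says.** All references are to the protocol article.

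- Section 2.3 (Outcomes): "The secondary outcomes are postoperative pain score and physical recovery". PROMIS measures "are used to evaluate physical function". No measurement time is given for either outcome, and no preoperative measurement is mentioned.
- Section 2.4 (Statistical analysis): "Continuous and categorical variables are analyzed using χ^2^-tests and independent t-tests, respectively". The pairing is the wrong way round. Put right, a continuous score gets an independent t-test. No covariate, change score or model appears.
- Section 2.4 also says "Intention to treat analysis is applied to evaluate the outcomes" and "Significant level: *P* < .05".
- Section 2 (Materials and methods): "The experiment is a single-center randomized clinical research".
- Section 2.1 (Inclusion and exclusion criteria): "In all, 50 patients with lumbar vertebral osteomyelitis (LVO) who prepares surgical treatment will be included in the study", and on follow-up, "All patients are followed up for at least 12 months". The allocation ratio is not stated.

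**The concern.** Section 2.4 names the tests, so the analysis of these scores is a stated choice. Once the pairing is corrected, that choice is a plain two-sample comparison.

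This matters for two reasons. First, any variation in the postoperative score that the preoperative score could explain stays in the error term. Second, in a trial of this size the arms can differ at baseline by chance, and an unadjusted difference carries part of that imbalance into the estimate. Pain and physical function are the outcomes here that rest on the patient's own report.

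Timing also counts. A preoperative score that is not taken before the operation cannot be recovered later, so the decision has to be made before patients are operated on.

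**Working it through.** **What can be reproduced.** The total of 50 comes without an effect size, SD, power or dropout rate, so the plan has no power figure of its own to check.

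**Inputs**
- From the article: N = 50; significance level 0.05.
- Assumed: 1:1 allocation, so n = 25 per arm; two-sided testing; a true difference of d = 0.6 SD; and r, the correlation between the preoperative and postoperative score, shown from 0.15 to 0.7.

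**Step 1: unadjusted t-test.**
- Noncentrality = d × √(n/2) = 0.6 × √12.5 = 2.121, with 48 degrees of freedom.
- Power = 0.547, or 55%.
- The 95% CI half-width is t(0.975; 48) × √(2/25) = 0.57 SD.

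**Step 2: variance under ANCOVA.**
- Adjusting for the preoperative value multiplies the variance of the group difference by 1 − r².
- Estimating one covariate costs a factor of about 1 + 1/(N − 4) = 1 + 1/46 = 1.022.
- The net factor is V = (1 − r²) × 1.022.
- Equivalent unadjusted sample size = 50/V.
- Noncentrality = 2.121/√V.

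| r | 1 − r² | V | Equivalent N | Noncentrality | Power at 0.6 SD |
|---|---|---|---|---|---|
| unadjusted | – | 1 | 50 | 2.121 | 55% |
| 0.15 | 0.978 | 0.999 | 50 | 2.123 | 55% |
| 0.2 | 0.960 | 0.981 | 51 | 2.142 | 56% |
| 0.3 | 0.910 | 0.930 | 54 | 2.200 | 58% |
| 0.5 | 0.750 | 0.766 | 65 | 2.423 | 66% |
| 0.7 | 0.510 | 0.521 | 96 | 2.939 | 82% |

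The gain is essentially nil at r = 0.15, about 3 points of power at r = 0.3, and substantial only from about r = 0.5.

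**Step 3: chance imbalance.** With 25 per arm, the standard error of a baseline difference is √(2/25) = 0.28 SD. A difference of 0.3 SD or more in either direction then arises in about 29% of randomizations (z = 0.3/0.283 = 1.06). Such a difference shifts the expected unadjusted estimate by r × 0.3 SD, which is 0.15 SD at r = 0.5. ANCOVA takes out the part that is linear in the measured baseline score.

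**The case against.** **Validity.** In a randomized trial the independent t-test is unbiased and keeps its type I error, and its standard error already allows for chance imbalance. This stands in full. A reader might infer that the unadjusted comparison is wrong or biased; the article gives no support for that.

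**What the outcomes mean.** A reader might also infer that physical recovery is by definition measured against the preoperative state, so that the stated test contradicts the outcome. Section 2.3 does not define the term. A t-test on change scores would fit the words of Section 2.4 and would use the preoperative value. The point is therefore firmer for the pain score, which is called postoperative, than for physical recovery.

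**Baseline spread.** It is tempting to argue that preoperative pain and function vary widely in these patients. The article gives no SD or range, so the argument here does not rely on that.

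**Size.** The correlation, the 0.6 SD difference and the equal allocation are all assumptions, and the large gains belong to the top of the range. This stands, which is why low values of r are shown.

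**Level of detail.** Covariate adjustment is often left to a full protocol or analysis plan, and an article condenses these. That has weight. Still, the article names its tests, and any later plan that used ANCOVA would depart from them.

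**Conclusion.** The point holds as a low-cost improvement in precision. Section 2.4 provides only unadjusted two-sample tests, and the article mentions neither a preoperative pain or PROMIS score nor adjustment for one.

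Under the stated assumptions the benefit ranges from almost nothing (r of about 0.15) to the equivalent of roughly 46 more patients at r = 0.7 (96 against 50). At r = 0.5 it is about 15 more patients and 11 points of power. Nothing in the article shows where in this range the trial would fall.

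Only secondary outcomes are affected, and the planned comparison would still be valid if left alone.

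**What to change.** 1. In Section 2.3, state that the pain score and PROMIS physical function are taken before surgery in every patient, and name one postoperative time point at which each is compared.
2. In Section 2.4, correct the pairing of tests and variable types. Then state that each score at its named time point is compared between arms by ANCOVA, with treatment group and the patient's preoperative value in the model, reporting the adjusted mean difference with its 95% CI.

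**Cost.** A few sentences of text, one degree of freedom per analysis and, if the scores are not already collected, one short preoperative questionnaire. No extra patients are needed. Scores missed before an operation cannot be obtained afterwards, so the change should be made before patients are operated on. If r proves low, little is gained, and the loss is limited to the covariate cost of about 2% in variance.
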